### Blinding

The information about treatment allocation is not given to the patient in order to ensure blinding as long as possible. However, due to the nature of the intervention, blinding of the patient during the intervention may be difficult. Blinding of the therapist is not possible.

### Data management

Data is collected by a blinded assessor using data based case report forms. All data are entered into an electronic database by a scientific staff member at the study site who is not involved in data collection. Original data forms will be kept on file at the study site in locked cabinets. Access to the study data will be restricted to authorized staff members. Incremental back-ups of the electronic database will be performed on a daily basis. The database is protected by a password.

After termination of the study and the data verification, all files will be archived for a period of 10 years.

### Statistical methods

Descriptive statistics including means and standard deviations or medians and 25th and 75th percentiles for continuous data, and frequencies for categorical data will be determined. The appropriateness of the randomization will be examined by testing for between group differences in demographical and clinical variables (e.g., age, time since stroke, SULCS score).

Among the cases available for analyses, intention-to-treat analyses will be performed. For all outcome measures, the within-subject differences between the baseline and post-test, and the baseline and follow-up test are of central interest in the intervention group compared to the control group. For the primary outcome measure, a repeated measures analysis of variance will be used. Pairwise comparisons will be generated using Tukey's method. A subgroup analysis will be performed to investigate the influence of lesion side. For the secondary ordinal outcome measures, non-parametric statistics will be used. Between-group comparisons (intervention vs. control group) will be performed to compare the short-term changes (baseline—post-test) and long-term changes (baseline—follow-up) between groups using Mann-Whitney *U*-tests. In addition within-group comparisons will be performed using Friedman tests. If the Friedman test showed significant differences, Wilcoxon matched-pairs tests will be used to compare baseline and post, and baseline and follow-up measures. Effect sizes (r) of changes between groups and within-groups will be calculated.

In addition, a per protocol analysis will be done, excluding patients who deviated from the protocol. Missing data will be replaced by the last value carried forward method.

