## Abstract

Stroke often affects arm functions and thus impairs patients' daily activities. Recently, several studies have shown that additional movement acoustics can enhance motor perception and motor control. Therefore, a new method has been developed that allows providing auditory feedback about arm movement trajectories in real-time for motor rehabilitation after stroke. The present article describes the study protocol for a randomized, controlled, examiner, and patient blinded superiority trial (German Clinical Trials Register, www.drks.de, DRKS00011419), in which the method will be applied to 13 subacute stroke patients with hemiparesis during 12 sessions of 30 min each as additional feedback during the regular movement therapy. As primary outcome, a significant pre-post-change in the Box and Block Test is expected that exceeds the performance increase of 13 patients who will be provided with sham-acoustics. Possible limitations of the method as well as the study design are discussed.

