### Objectives

The primary objective of this trial is to investigate the effectiveness of the above mentioned approach for real-time movement sonification on motor abilities of the paretic upper limb in subacute stroke patients. The hypotheses are that, compared to patients provided with an auditory control stimulus, patients provided with real-time movement sonification (1) improve gross motor dexterity of the paretic upper limb assessed with the Box and Block test, and (2) motor function of the paretic arm and hand measured with the Action Research Arm Test and the Stroke Upper Limbs Capacity Scale.

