### Outcomes

Primary outcome measure is the Box and Block Test (44). The test is a measure of unilateral gross manual dexterity. It counts the number of wooden blocks that can be transported from one compartment of a box to another compartment within 1 min. The Box and Block test shows high test-retest and interrater reliabilities in elderly subjects and subjects with neurological disorders (45, 46). The construct validity of the test is high when compared with the ARAT and the Fugl-Meyer test (45, 46). The Box and Block test is suitable to detect changes over time in stroke patients (47).

Secondary outcome measures are the Action Research Arm Test (ARAT) and the Stroke Upper Limbs Capacity Scale (SULCS). The ARAT assesses mainly the ability to handle smaller and larger objects with a variety of qualitatively rated items. It includes four subtests: grasp (6 items), grip (4 items), pinch (6 items), and gross movement (3 items). The scores for each item range from 0 to 3. We use the standardized protocol published by Yozbatiran et al. (48) to assess the ARAT. The test shows high intrarater reliability and interrater reliability. Validity is high when compared to the Fugl-Meyer test and it is sensitive to detect changes (47).

The SULCS assesses the capacity of the paretic upper limb in stroke patients. It consists of 10 items which represent tasks that are related to daily activities (49). The items assess proximal arm capacity without need for active wrist or finger movement (3 items), arm capacity combined with basic hand capacity (grasp tasks without manipulating, 4 items), and advanced hand capacity (manipulating tasks, 3 items). The scale has good interrater reliability and a high construct validity when compared with the ARAT and the Rivermead Motor Assessment (RMA) (50).

All these outcome measures are assessed at baseline before the start of the intervention, at post-test after the last intervention, and at follow-up test 2 weeks after the end of the intervention. The measures are assessed by an assessor blind to treatment allocation. The assessor is experienced and trained in performing the clinical assessments.

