### Sample size

The sample size calculation for this trial is based on the pilot study by Schmitz et al. (34) investigating the feasibility of movement sonification in stroke patients. The study found a small, but statistically significant effect and a high correlation between the number of blocks which were transported in the Box and Block test before and after five 20-min sessions with movement sonification. As the intervention period is much longer in this trial, we assume a medium effect. For an effect size of *f* = 0.2, a correlation among repeated measures of 0.7, a power of 80%, and a significance level of α = 0.05 a total sample size of 26 subjects is required. The sample size calculation was performed using G^*^Power.

A dropout rate of 20% was anticipated, consequently a minimum number of 32 subjects has to be enrolled in the study.

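### The primary question is a group difference in baseline-to-post change, but the plan names no test for it, and N = 26 and its 80% power fit a three-time-point interaction instead

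*Protocol article*

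**What the plan says.** The Abstract puts the primary question as a comparison of pre-post gains: "As primary outcome, a significant pre-post-change in the Box and Block Test is expected that exceeds the performance increase of 13 patients" given sham-acoustics. The Objectives section states the matching hypothesis, that patients given sonification "improve gross motor dexterity of the paretic upper limb assessed with the Box and Block test" relative to the auditory control, but names no time point.

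The Outcomes section gives three assessments: "All these outcome measures are assessed at baseline before the start of the intervention, at post-test after the last intervention, and at follow-up test", the last of them 2 weeks after the intervention ends.

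The Statistical methods section says that, for every outcome, "the within-subject differences between the baseline and post-test, and the baseline and follow-up test are of central interest" in the comparison of the two groups. It then says "For the primary outcome measure, a repeated measures analysis of variance will be used" and "Pairwise comparisons will be generated using Tukey's method". It does not state the number of time levels in the ANOVA, the term or contrast that decides the trial, or the means to which Tukey's method applies.

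The Sample size section takes f = 0.2, a correlation of 0.7 among repeated measures, 80% power and α = 0.05, and concludes in G*Power that "a total sample size of 26 subjects is required". It names neither the test nor the number of measurements. With 20% dropout it enrols at least 32.

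**The concern.** The Abstract asks one question with one degree of freedom: does the baseline-to-post change differ between the groups? The analysis section answers a wider one.

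- With three time points and two groups, the interaction has 2 df. It is sensitive to any difference between the two time profiles, including one that appears only at follow-up.
- A group difference in change involves four means: two groups at two times. A pairwise comparison involves two. So Tukey comparisons do not test the Abstract's hypothesis, whether they are made between time points, between groups or between group-by-time cells.
- The two changes are listed side by side, and nothing says which one the primary conclusion rests on.

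Two things are at stake. The result that counts as success could be settled after the data are seen. And the stated 80% power may belong to a test other than the one a reader of the Abstract expects.

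**Working it through.** **Inputs.** From Sample size: f = 0.2, ρ = 0.7, α = 0.05, power 80%, N = 26. From Trial design: k = 2 groups, 1:1. From Outcomes: three measurements. Assumptions: the F test is two-sided in effect, and correlations are equal (sphericity holds).

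**Formula** for the group-by-time interaction with m measurements, as in G*Power:

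λ = f²·N·m/(1−ρ), df1 = (k−1)(m−1), df2 = (N−k)(m−1); power = P(F′(df1, df2, λ) > F critical).

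**Step 1: reproduce the stated N.** With m = 3 and N = 26, λ = 0.04·26·3/0.3 = 10.4, df = 2 and 48, critical F = 3.19, power 80.6%. With N = 24, power is 76.9%. So 26 is the smallest even total, and the stated figure fits the three-measurement interaction. The main effect of time with m = 3 also gives 26, but it does not compare groups. The between-group main effect with m = 3 needs 160.

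**Step 2: same inputs, pre-post only.** With m = 2 and N = 26, λ = 0.04·26·2/0.3 = 6.93, df = 1 and 24, critical F = 4.26, power **71.5%**. N = 30 gives 77.9% and N = 32 gives 80.7%.

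Cross-check as a t test on change scores: the group difference in change is 4f = 0.80 SD, and the SD of change is √(2·0.3) = 0.775 SD. The noncentrality is 0.80/(0.775·√(2/13)) = 2.63, with 24 df, and power is again 71.5%.

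**Step 3: f = 0.2 read as the three-time-point interaction.** Let the group difference be δ·(0, a, b) at baseline, post and follow-up. Then f² is the mean of [(δ/2)·(profile − its mean)]². Solving for δ at f = 0.2 and testing only the pre-post change at N = 26:

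| Profile of the group difference | Pre-post difference (SD) | Pre-post power |
|---|---|---|
| Gain fully kept at follow-up (0, 1, 1) | 0.85 | 76% |
| Gain fully lost at follow-up (0, 1, 0) | 0.85 | 76% |
| Half kept (0, 1, 0.5) | 0.98 | 87% |
| Linear build-up (0, 0.5, 1) | 0.49 | 34% |

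If between about 10% and 90% of the gain is kept, pre-post power is 80% to 87%. All four profiles have 80.6% power on the omnibus interaction. So does a profile with an effect at follow-up only (0, 0, 1), where there is no pre-post difference to detect.

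**Step 4: a single baseline-adjusted contrast at post-test.** The residual SD is √(1 − 0.7²) = √0.51 = 0.714, with n = 13 per group and 23 df. For 0.80 SD the noncentrality is 0.80/(0.714·√(2/13)) = 2.86, power 78.1%. For 0.85 SD it is 3.03, power 82.7%.

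**The case against.** The planned ANOVA and the sample size agree with each other: the outcome is measured three times, and 26 is the right answer for that interaction. The interaction does compare change between groups, and the choice of contrast is often left to an analysis plan, which is not shown here. All of this stands, so it would be wrong to infer that the plan contains no between-group test of the primary outcome. What remains is a mismatch inside the document. The Abstract fixes a pre-post question, and the test and sample size fixed elsewhere answer a different one.

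A reader might also infer that the trial has 71% power, full stop. That holds only if f = 0.2 is the pre-post effect. This reading is reasonable, because the Sample size section starts from a before-and-after pilot comparison, but it is not stated. A one-sided 5% pre-post t test would have 81.9% power at 26, but no one-sided test is planned and the ANOVA F test offers none. If all 32 enrolled were analysed with carried-forward values, nominal power would be 80.7%, ignoring any dilution from those values. The protocol nevertheless sizes on 26, and the Abstract on 13 per group.

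Three further inferences are not supported.

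- Inflated family-wise error from two unadjusted 5% tests: the plan does not say that it will test the two changes separately and unadjusted.
- A specific loss of power under Tukey: that needs a set of means and an error term that the plan does not give.
- A route to claiming primary success from within-group tests: the sentence "In addition within-group comparisons will be performed using Friedman tests" belongs to the secondary ordinal outcomes and stands beside between-group Mann-Whitney tests.

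**Conclusion.** The point holds in this form. The Abstract's primary question is the group difference in baseline-to-post change. The analysis section names no deciding test for it, leaves two changes unranked, and relies on an omnibus test that follow-up alone can make significant. The stated 80% does not belong to the pre-post comparison. At 26 analysed, power is 71.5% if f = 0.2 and ρ = 0.7 describe the pre-post effect. If f = 0.2 is the interaction over three times, power is about 34%, 76% or 87% depending on a profile that the protocol does not state.

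These figures assume equal correlations, a two-sided 5% level and 13 analysed per group. That the ANOVA uses three time points is itself an inference, from the assessment schedule and from the exact reproduction of 26. A reader might conclude that follow-up is a co-primary endpoint. No section says so: the sentence that lists both changes covers all outcomes, secondary ones included. The defect is a missing ranking.

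**What to change.** Replace the primary analysis sentences with wording such as: *The primary analysis is the between-group difference in Box and Block score at post-test, adjusted for baseline, as one 1-df contrast at a two-sided 5% level with a 95% confidence interval. The follow-up contrast is secondary.* Do not use Tukey pairwise comparisons for the primary conclusion. An unadjusted contrast of change scores would also cure the defect. Baseline adjustment is preferred because it recovers most of the power from data already being collected.

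Restate power at 26 analysed together with its assumption: about 71% for the unadjusted change at 0.80 SD, or about 78-83% baseline-adjusted for 0.80-0.85 SD.

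The cost is an amendment of the protocol and registry wording, by the route in the Protocol amendments section, before the allocation schedule is opened for the primary analysis. No new measurements are needed. The follow-up change loses its equal standing, and the power statement becomes conditional. If the unadjusted change were kept and 80% power required under the same inputs, 32 analysable patients would be needed, or 32/0.8 = 40 enrolled at the stated dropout.

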All patients included in the study are inpatients at the rehabilitation hospital and receive the normal therapy setting during the study period. The only intervention which is prohibited during the intervention period is robot-assisted training for the upper extremities.

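### The added within-arm Friedman and Wilcoxon tests on ARAT and SULCS measure recovery shared by both arms, not the sonification effect, and are better replaced by descriptive summaries

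*Protocol article*

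**What the plan says.** Under Objectives, both hypotheses are between-group: the expected improvement is stated as "compared to patients provided with an auditory control stimulus". Hypothesis 2 covers ARAT and SULCS.

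Under Statistical methods, the baseline-to-post and baseline-to-follow-up changes in all outcome measures "are of central interest in the intervention group compared to the control group". For the two ordinal secondary scales, these changes are compared between arms with Mann-Whitney tests. The section then adds three within-arm elements:

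- An omnibus test over the three time points in each arm: "In addition within-group comparisons will be performed using Friedman tests".
- A conditional second step, taken only after a positive omnibus result: "If the Friedman test showed significant differences, Wilcoxon matched-pairs tests will be used to compare baseline and post, and baseline and follow-up measures".
- A measure of magnitude for each arm as well as for the contrast: "Effect sizes (r) of changes between groups and within-groups will be calculated".

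Under Interventions, both arms receive upper-limb training on 4 days a week for 3 weeks (12 sessions), and all patients "receive the normal therapy setting during the study period". Eligibility is 4 weeks to 6 months after stroke. No sentence labels the within-arm tests as descriptive, and no sentence draws a conclusion about efficacy from them.

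**The concern.** A within-arm Friedman or Wilcoxon test has no comparator. Its null hypothesis is no change over time, which is implausible in either arm of this trial, because spontaneous recovery, normal inpatient therapy and 12 training sessions all act in both. Rejecting that null says nothing about sonification against sham.

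The practical risk comes from the pattern of results. With 13 patients per arm, one arm can easily reach p < 0.05 while the other does not, even if both recover equally. Printed beside a non-significant Mann-Whitney result, an improvement that is significant in the sonification arm only invites a conclusion that the randomised comparison does not support. ARAT and SULCS are open to this because the sample size was set for the Box and Block Test, so a non-significant between-group result on these scales is quite possible even if the treatment works.

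**Working it through.** **Arm size, from the plan's own figure.** The Sample size section gives f = 0.2, correlation 0.7, power 80%, alpha 0.05 and a total of 26. For the group-by-time interaction with 2 groups and 3 measurements:

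- noncentrality = f² × N × m / (1 − ρ) = 0.04 × 26 × 3 / 0.3 = 10.4
- degrees of freedom = (2 − 1)(3 − 1) = 2 and (26 − 2)(3 − 1) = 48
- power = 0.806

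The stated 26 is reproduced, which with 1:1 allocation gives 13 per arm. The plan states no power or error rate for ARAT or SULCS.

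**Number of tests.** Within arms: 2 scales × 2 arms = 4 Friedman tests, and up to 2 × 2 × 2 intervals = 8 Wilcoxon tests. Between arms: 2 scales × 2 intervals = 4 Mann-Whitney tests.

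**General result.** If each arm has the same probability p of a significant within-arm test, exactly one arm is significant with probability 2p(1 − p), at most 50% (at p = 0.5). The sonification arm alone is significant with probability p(1 − p), at most 25%. This holds for any test.

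**Simulation of the planned sequence.** Friedman over three time points, then Wilcoxon on baseline to post only if Friedman is significant, each at two-sided 0.05; Mann-Whitney on the same change. 13 per arm, 2,500 runs, and the same true shift at post and follow-up in both arms. These inputs are assumptions: normal scores, correlation 0.7 (borrowed from the Box and Block calculation), and the size of the common recovery, which the documents do not give.

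The shift was set in SD of the score. The SD of change is √(2 × (1 − 0.7)) = √0.6 = 0.775 of that, so a shift of 0.6 SD of score is 0.6 / 0.775 = 0.77 SD of change. By symmetry, sonification only is half of one arm only.

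| Common recovery, SD of score | SD of change | One arm only | Sonification only (half) | Both arms | Mann-Whitney significant |
|---|---|---|---|---|---|
| 0 | 0 | 4% | 2% | 0% | 4.5% |
| 0.3 | 0.39 | 22% | 11% | 2% | 4.7% |
| 0.4 | 0.52 | 37% | 18% | 6% | 4.0% |
| 0.5 | 0.65 | 46% | 23% | 16% | 3.9% |
| 0.6 | 0.77 | 49% | 25% | 30% | 4.0% |
| 0.8 | 1.03 | 27% | 14% | 69% | 4.8% |
| 1.0 | 1.29 | 7% | 3% | 93% | 5.0% |

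Check against the formula at 0.77 SD of change: p = both + half of one only = 0.301 + 0.245 = 0.546, so p(1 − p) = 0.546 × 0.454 = 0.248, against 0.245 simulated.

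**Separate runs with the recovery set directly in SD of change**, same gate and assumptions:

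| Common recovery, SD of change | Sonification only |
|---|---|
| 0.4 | 12% |
| 0.6 | 22% |
| 0.8 | 24% |
| 1.0 | 16% |
| 1.2 | 7% |
| 1.5 | under 1% |

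Sonification only together with a non-significant Mann-Whitney test occurs in 11%, 20% and 22% of trials at 0.4, 0.6 and 0.8 SD.

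**Effect of the gate.** Without the Friedman step, sonification only would be about 18-19%, 25% and 19-20% at 0.4, 0.6 and 0.8 SD. The gate lowers the figure for small recoveries and raises it at 0.8 SD.

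**Reading of the tables.** The within-arm result moves with the amount of recovery, although the treatment difference is zero throughout. The between-group test stays at about 4-5%.

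**Between-group test.** Under the same assumptions, rank ANCOVA on the baseline score gains about 2-5 points of power over Mann-Whitney on change, with type I error near 5%.

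**The case against.** The strongest reply is that the plan already ranks its analyses correctly. The hypotheses are between-group, the contrast of central interest is between-group, the Mann-Whitney tests come first, and the within-arm tests are introduced as an addition. Only secondary outcomes are involved; the Box and Block analysis and the sample size are untouched. All of this stands, and it makes the point minor.

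Three stronger readings are tempting, and the documents do not support them.

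- *The trial will claim efficacy from a result in one arm only.* No sentence says so. The 12-24% is therefore not a type I error of the plan. It would become one only if that pattern were used as a decision rule, which the protocol does not adopt.
- *The Mann-Whitney test ignores the baseline score.* It does not: change is the later score minus baseline. What is absent is covariate adjustment for baseline, and the test is valid without it.
- *The rank test should be stratified by the randomisation factors.* Age group by lesion side gives 2 × 2 = 4 strata. 26 / 4 = 6.5 patients per stratum, about 3 per arm, is too thin to insist on a van Elteren test.

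It is also fair to object that 0.4-0.8 SD is not a documented recovery and surrounds the peak of the curve. With larger recovery the one-arm pattern becomes rare. Both arms are then significant, however, and the test still carries no information on sonification.

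**Conclusion.** The point holds as a minor one. The within-arm tests are planned, they do not address hypothesis 2, and nothing in the text marks them as descriptive. With no treatment difference, sonification only appears in about 12-24% of trials per scale and interval at a common recovery of 0.4-0.8 SD of change, falling to about 16% at 1.0 SD and 7% at 1.2 SD; Mann-Whitney stays near 5%.

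The percentages are illustrative. They rest on normal scores for scales that are ordinal, a correlation borrowed from another outcome, and an assumed recovery. The bound p(1 − p) ≤ 25% and the lack of a comparator need none of these. The consequence is a risk of misinterpretation on secondary outcomes, not a fault in the planned between-group inference.

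**What to change.** Replace the within-arm Friedman and Wilcoxon tests with descriptive reporting of change in each arm, as medians with 25th and 75th percentiles, the format that the Outcomes section already provides for. Give no within-arm p-values. State that conclusions on ARAT and SULCS rest only on the between-group comparison.

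A worthwhile but optional addition is to replace Mann-Whitney on change with a rank ANCOVA on the baseline score, which is already collected, for the small gain in power shown above.

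The cost is a few lines of wording and slightly different analysis code. The downside is that within-arm p-values, which some readers expect, would not be reported. No planned between-group result changes if only the within-arm tests are removed.

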## Methods

### Study setting and eligibility criteria

All subjects included in the study are inpatients at a rehabilitation hospital in Germany. They meet the following inclusion criteria: hemiparesis of the upper extremity (SULCS score ≥3) after a unilateral ischemic or hemorrhagic stroke (4 weeks to 6 months after stroke onset), the functional ability to pick up a wooden cube (2.5 cm in size) with the paretic hand, and age between 18 and 80 years. Patients with unstable fracture, the inability to sit for 30 min, or severe aphasia or cognitive impairment, which compromises the implementation of the assessments or the therapy are excluded from the trial.

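### Last value carried forward, the only missing-data method named, records no recovery for patients without a post-test; it shrinks a true effect and lets unequal loss look like a group difference

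*Protocol article*

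**What the plan says.** The Statistical methods section of the protocol article names one missing-data method, without limiting it to an outcome or an analysis set: "Missing data will be replaced by the last value carried forward method". The sentence just before it introduces a second analysis set: "In addition, a per protocol analysis will be done, excluding patients who deviated from the protocol". Earlier in the same section the main set is described: "Among the cases available for analyses, intention-to-treat analyses will be performed". The article does not define availability.

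The analysis rests on change from baseline: "the within-subject differences between the baseline and post-test, and the baseline and follow-up test are of central interest". For the Box and Block Test, "For the primary outcome measure, a repeated measures analysis of variance will be used". Besides baseline, outcomes are measured "at post-test after the last intervention, and at follow-up test 2 weeks after the end of the intervention" (Outcomes).

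Patients enter "4 weeks to 6 months after stroke onset" (Study setting and eligibility criteria). Both arms train the arm and also receive usual inpatient therapy (Interventions), and the abstract expects the sham group to improve too. On losses, "A dropout rate of 20% was anticipated" (Sample size). Patients who stop the intervention stay on the measurement schedule (Interventions), so gaps arise from withdrawal or missed assessments.

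**The concern.** Carrying a value forward assumes that nothing changes after the last measurement. Here that assumption conflicts with what the article expects. A patient lost before the post-test has only a baseline to carry, so both changes of central interest become zero although recovery is expected in either arm. A patient lost after the post-test has that value copied, so the follow-up change shows full retention whether gains continued or faded.

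These values enter the primary comparison as if they had been observed. At stake are the size of the estimated effect, the power of a trial of 32 patients and, if loss differs between arms, the type I error. Unequal loss is conceivable: the Discussion says that patients are told the sham sound is unrelated to their movements and that some may notice their group. The article gives no loss figures by arm.

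A second, lesser problem is that the availability wording and the carry-forward rule are not reconciled, so a reader cannot tell which patients the primary analysis contains.

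**Working it through.** **The plan's own figure.** Inputs from Sample size: f = 0.2, correlation 0.7, power 80%, α = 0.05. For the group-by-time interaction with k = 2 groups and m = 3 visits, λ = N·m·f²/(1−ρ), df1 = (k−1)(m−1), df2 = (N−k)(m−1). N = 26 gives power 0.806 and N = 24 gives 0.769, so 26 is reproduced. Twenty per cent of the 32 enrolled is 6.4 patients.

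**The effect implied by f = 0.2.** If a group difference δ (in SD of the score) is present at post-test and held at follow-up, the interaction terms are ±(δ/2)(−2/3, 1/3, 1/3). Their mean square is δ²/18, so δ = 0.2·√18 = 0.85.

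**Expected estimate under carry-forward.** Let R be mean control recovery, and p_I and p_C the fractions without a post-test, lost at random:

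(1−p_I)(R+δ) − (1−p_C)R = δ(1−p_I) − (p_I−p_C)R

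- Equal 20% loss: 0.85 × 0.8 = 0.68, a 20% shrinkage that does not depend on R.
- Equal loss, δ = 0: the expression is zero, so there is no bias.
- δ = 0, 10% intervention and 30% control: 0.2·R, that is 0.10, 0.16 and 0.24 SD for R = 0.5, 0.8 and 1.2. The sign reverses if the arms are swapped.

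**Power, two-visit change comparison.** Assumptions: 16 per group, all losses before the post-test, R assumed (the article gives no value). The variance of a change is 2(1−0.7) = 0.6. Mixing in zeros, the variance in an arm with mean change μ is (1−p)·0.6 + p(1−p)μ², which is 0.48 + 0.16μ² at p = 0.2.

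| R | Variance, control | Variance, intervention | SE of difference | 0.68/SE | Simulated power |
|---|---|---|---|---|---|
| 0.5 | 0.520 | 0.772 | 0.284 | 2.39 | 63% |
| 0.8 | 0.582 | 0.916 | 0.306 | 2.22 | 56% |
| 1.2 | 0.710 | 1.152 | 0.341 | 1.99 | 47% |

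The critical t on 30 df is 2.04, so the ratios agree with the simulated power. Using observed changes only (about 12.8 per arm), SE = √(2 × 0.6/12.8) = 0.306 and 0.85/0.306 = 2.78; simulated power is 74% to 75%, or 79% with baseline adjustment.

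**Type I error.** With 10% against 30% loss, δ = 0 and the same settings, simulation gives about 7% at R = 0.5, 9% at 0.8 and 12% to 13% at 1.2. With equal 20% loss it stays at 5%.

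**Sensitivity to the assumed effect.** With f = 0.2 read on two visits, δ = 4 × 0.2 = 0.80. Equal 20% loss then gives 0.64, with power 59%, 49% and 39% for R = 0.5, 1.0 and 1.5, against about 70% with observed changes. With 30% intervention and 10% control loss the estimate is 0.46, 0.36 and 0.26; with the arms swapped it is 0.82, 0.92 and 1.02.

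**Sensitivity to timing and test.** This uses the three-visit group-by-time analysis of variance, δ = 0.85, R = 0.5, 0.8 and 1.2, and recovery assumed flat after the post-test, which favours carry-forward:

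- All losses before the post-test, 20% per arm: power 70%, 62% and 55%.
- Half the losses only at follow-up: power 79%, 75% and 71%; type I error at 10% against 30% loss is about 5% to 7%.
- All losses only at follow-up: power about 89%, type I error about 5%.

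**The case against.** The strongest case against concerns the extent of the harm.

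- **Timing and test.** The headline figures put every loss before the post-test and test only the baseline-to-post change, whereas a three-visit analysis is planned. Treatment lasts three weeks in inpatients, and patients who stop it are still measured, so some losses may fall only at follow-up. The article gives no split. This stands: the figures are an early-loss illustration, and the harm is much smaller with mixed timing.
- **Imbalance.** A threefold difference in loss between arms has no support in the article. This stands: the type I figures show what the rule permits and do not forecast this trial.
- **The comparator.** Observed-data results look unbiased because loss was simulated at random. The article's reasons for stopping include new disease or complications; if such patients also leave the study, missingness may be informative and observed-data methods can be biased too. This stands, and is why a sensitivity analysis is needed.
- **A contradiction?** A reader might infer that the carry-forward rule contradicts the availability wording and that the 20% allowance implies a third analysis set. The text does not support this. Available cases can mean patients with some data, analysed as randomised, whose missed visits are then filled. The rule also follows the per protocol sentence directly and could belong only there. Inflating 26 to 32 is routine planning and defines no analysis set. What stands is that the rules are not reconciled.

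None of this rescues the method for patients without a post-test. Because the direction of bias under unequal loss is unknown in advance, it cannot be defended as reliably conservative either.

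**Conclusion.** The concern holds as a poor choice of method that should be fixed. The article states carry-forward as its only rule, so this is not detail left to a statistical analysis plan.

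The proportional shrinkage of a true effect equals the fraction of intervention patients without a post-test when loss is equal and random: 20% if the whole anticipated dropout falls there. The power and type I figures rest further on assumed control recovery, early loss and a two-visit comparison.

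Two stronger readings go too far. Carry-forward does not freeze every dropout at baseline: those missing only the follow-up keep their post-test value. Nor does it always bias the comparison: with equal random loss and no true effect there is none. If carry-forward was meant only for the per protocol analysis, the distortion is confined to that analysis and the article then names no missing-data rule for the primary one.

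**What to change.** Replace the carry-forward sentence with wording such as:

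> Patients are analysed in the group assigned. The primary analysis is a likelihood-based mixed model for repeated measures using all observed Box and Block values (baseline, post-test, follow-up), including those collected after stopping the intervention, with no single imputation.

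Replace the availability wording with a definition: the set includes every randomised patient with at least one observed value. A patient with only a baseline is then in the model but adds no direct information on change, and the text should say so. Multiple imputation would also be defensible.

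Keep carry-forward at most as a labelled sensitivity analysis, beside a delta-adjusted one, because missingness may be informative. The present sentence also covers the ordinal secondary outcomes, so state their rule separately.

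The cost is a few sentences and standard software. No extra visits or data are needed, because patients who stop the intervention are already measured on schedule.
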